#### Objective 2: Assess safety of using a special wireless monitoring system in neonates

A dermatologist will score photographs of the patient skin prior to device placement, and following device removal, using Neonatal Skin Condition Score (NSCS) (Lund & Osborne, 2004). Before and after photograph pairs will be randomized prior to evaluation NSCS scores can range from 3 = intact condition skin to 9 = very poor condition skin. Any change of score from baseline to device removal (
}{}${{\rm \Delta}_{NSCS}} = NSC{S_{removal}} - NSC{S_{baseline}})$ will be reported as part of the sensor safety analysis. A one sample Wilcoxon test will be performed to determine if the mean change NSCS scores (
}{}$\overline {{{\rm \Delta}_{NSCS}}} )\;$are statistically different than 0 indicating no change in score from baseline.

Safety will also be assessed by evaluating the subjective pain scores obtained with the NIPS results. The average score will be reported, and any score of 3 or greater will be counted as indicative of pain. The total number of scores of 3 or more will be reported. Additionally, a one sample Wilcoxon test will be performed to determine if the average obtained NIPS score is below 3.

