### Sample size

A convenience sample size of 48 neonates was determined, 24 infants for each phase. However, after data is collected from the first 10 patients, an interim analysis will be performed to determine the precision of measurements between the Phillips and the ANNE^®^ One sensors for each of the parameters. Following that, a reassessment of the appropriate sample size will be performed based on this analysis.

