#### Device data collection forms

Two predefined data collection (DCF) forms will be used and are included as Supplemental Material (Additional File 4). The forms will provide specification of device placement, infant body position, concurrent therapeutic treatments, room temperature & humidity (RH32-C2; Omega Engineering, Norwalk, CT, USA), hourly axillary temperature measured by bedside nurse and other details which may be relevant when analyzing the data.

These DCF also include a section for reporting any adverse events such as skin irritation, erosion, or bleeding occurring during participation in the study.

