### Data monitoring and harms

The wireless devices utilized have been piloted before in NICU babies and are designed to adhere more gently to the skin than the adhesives used in standard of care, and thus will not cause additional risk or discomfort. Further, participation in this study will not interfere with the standard of care received. Patient participation can be stopped at any point if parents desire or upon decision of the attending physician (ex: in case of clinical deterioration). In the event of an adverse event such as skin erosion, bruising, bleeding or other it will be reported in the DCF as well as submitted to the McGill University Health Center’s Research Ethics Board to respect the protocol and Good Clinical Practice.

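### The only significance test for skin safety compares the average NSCS change with 0. A non-significant result would say little about safety, and the test puts no upper limit on the share of infants harmed.

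*Protocol article*

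**What the plan says.** In the protocol article, Statistical methods, Objective 2, a dermatologist scores photographs taken before placement and after removal. The scale is given as "NSCS scores can range from 3 = intact condition skin to 9 = very poor condition skin". The change is the score at removal minus the score at baseline, and any such change "will be reported as part of the sensor safety analysis". The inferential step follows: "A one sample Wilcoxon test will be performed to determine if the mean change NSCS scores" are "statistically different than 0 indicating no change in score from baseline". The section gives no significance level, no exact or large-sample version, no acceptable injury rate and no margin. It does not say whether the unit is the infant or the photograph pair, or whether the phases are pooled.

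Skin events are also captured outside this test. Under Device data collection forms: "These DCF also include a section for reporting any adverse events such as skin irritation, erosion, or bleeding". Under Data monitoring and harms: "In the event of an adverse event such as skin erosion, bruising, bleeding or other it will be reported in the DCF", with submission to the Research Ethics Board.

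Under Sample size: "A convenience sample size of 48 neonates was determined, 24 infants for each phase". After the first 10 patients, "a reassessment of the appropriate sample size will be performed based on this analysis"; that analysis concerns measurement precision between the two systems, not skin safety.

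**The concern.** Skin harm from a sensor is likely to affect a few infants while most show no change, partly because an infant who starts with intact skin (score 3) can only stay there or get worse. A signed-rank test drops the zero changes, so its information comes only from the infants whose score moved. If few move, it cannot reject, however badly those few are affected.

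Safety is one of the three study objectives and part of the primary outcome in the Abstract. Before wider use, a reader needs to know how high the injury rate could plausibly be, given what was seen. A p-value against 0 does not answer that, and non-rejection in a convenience sample can be mistaken for reassurance. The same section handles pain more directly: besides its own Wilcoxon test, it counts NIPS scores of 3 or more. It specifies no corresponding count or proportion for skin.

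**Working it through.** **Inputs from the protocol article.** 48 infants, 24 per phase (Sample size; Table 1: eight subgroups of 6, and 8 × 6 = 48). One-sample Wilcoxon test against 0 (Statistical methods, Objective 2). The sample size has no power calculation behind it, so there is no figure of that kind to reproduce.

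**Assumptions, because the article does not state them.** Two-sided 0.05 (the wording about differing from 0 reads as two-sided), exact test, one value per infant, no infant improving. The article gives no injury rate, so a range of 5% to 25% is shown.

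**Step 1: smallest attainable p-value.** If k infants have a non-zero change and all worsen, only one of the 2^k sign patterns is as extreme in that direction. The exact two-sided p is therefore 2 × 0.5^k.

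- k = 4: 2 × 0.0625 = 0.125
- k = 5: 2 × 0.03125 = 0.0625
- k = 6: 2 × 0.015625 = 0.031

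The size of the changes does not enter: five infants going from 3 to 4 and five going from 3 to 9 both give 0.0625. At least six worsened infants are needed. Five is 5/48 = 10.4% of the full sample, or 5/24 = 20.8% of one phase.

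**Step 2: chance of a non-significant result.** This is P(X ≤ 5), with X binomial(n, true rate):

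| True rate of worsening | n = 48 | n = 24 |
|---|---|---|
| 5% | 96.8% | 99.9% |
| 10% | 65.3% | 97.2% |
| 12.5% | 43.5% | 93.0% |
| 15% | 25.4% | 86.1% |
| 20% | 6.2% | 65.6% |
| 25% | 1.0% | 42.2% |

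The chance crosses 50% at a rate of about 11.7% for n = 48 and about 23.3% for n = 24.

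**Step 3: sensitivity to the assumptions.**

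- One-sided exact test: k = 5 gives 0.5^5 = 0.031, so the largest number that cannot reach significance is 4.
- Normal approximation, equal changes, tie correction, no continuity correction: z reduces to √k. For k = 3, z = 1.73 and p = 0.083; for k = 4, z = 2 and p = 0.046. The blind range is then 3 infants. With continuity correction, p is 0.072 at k = 4 and 0.037 at k = 5, so it is 4.
- Some infants improve: if 5% improve (equal-sized changes), the chance of a significant worsening with n = 48 is 6.4%, 22.8% and 45.6% at worsening rates of 10%, 15% and 20%. With none improving it is 34.7%, 74.6% and 93.8%.
- Photograph pairs as the unit: with one pair per sensor per day (an assumption), phase 1 gives 24 × 4 × 2 = 192 pairs and phase 2 gives 24 × 4 × 3 = 288. Five injured infants could then give more than five non-zero changes. But pairs from one infant are correlated and the test assumes independence, so the p-value would not be valid.

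**Step 4: what an interval would say.** Exact (Clopper-Pearson) 95% limits. With no events, the upper limit is 1 − 0.025^(1/n).

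- 0/48: upper limit 7.4%
- 0/24: upper limit 14.2%
- 5/48 = 10.4%: 3.5% to 22.7%
- 5/24 = 20.8%: 7.1% to 42.2%

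**The case against.** A reader might infer that injuries would be written up as no change, or that a real injury rate anywhere from 10% to 20% would usually be missed. The document does not support either reading.

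- Any NSCS change is to be reported, skin events go on the data collection form, and adverse events go to the ethics board. Five injured infants would be visible whatever the p-value.
- In the quoted sentence, the words about no change most naturally explain what the value 0 means. The article does not say that non-significance will be taken as proof of safety.
- With all 48 infants, the test would probably detect a rate of 15% or 20% under the stated assumptions. The 20% figure applies only if a phase of 24 is tested alone, which the article does not say will be done.
- The five-infant limit depends on the version of the test and the unit of analysis, both left open.
- This is an exploratory observational study, its Discussion acknowledges the convenience sample as a limitation, and an article commonly leaves confidence intervals to a fuller document.

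All of this stands, and it limits the size of the point. It does not remove it. Listing events does not bound their rate, and the concern rests on the test that the article does state, not on an interval that it leaves out. The other versions of the test shrink the blind range without closing it.

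**Conclusion.** The point holds in a limited form. The one inferential skin-safety analysis stated in the article is poorly matched to an uncommon harm: its non-significance would carry little information, and it gives no upper limit on the share of infants affected. Under an exact two-sided 0.05 test with one value per infant and nobody improving, five worsened infants cannot reach significance. Non-significance is the likelier outcome below about 12% with 48 infants, or below about 23% with a single phase of 24. These thresholds are conditional on choices that the article does not state, and on the planned sample size remaining unchanged after the reassessment. The injuries themselves would not be hidden. This is a recommended, inexpensive improvement and not a flaw that must be corrected before the study can proceed.

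**What to change.** Make the main skin-safety result the number and proportion of infants with an NSCS rise of 1 or more at any sensor site, or a skin event on the data collection form. Report it with an exact 95% confidence interval, overall and by phase, and use the upper limit as the safety statement. Name the infant as the unit of analysis, so that several sensors and time points in one infant count once. Keep the Wilcoxon test as supportive, with a sentence saying that a non-significant result is not to be read as absence of harm.

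The photographs, scores and event forms are already part of the plan, so only the analysis wording changes. The price is a less favourable-looking statement: even with no affected infants, the upper limit would be 7.4% for 48 infants and 14.2% for 24.

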#### Objective 2. Assess safety of using a special wireless monitoring system in neonates

Safety will be assessed by reporting any adverse skin reactions to sensors as well as evaluating pain at the time of device removal.

Skin Evaluation: Prior to device placement and following removal, photographs of the skin at the site of device placement will be taken. A board-certified dermatologist will evaluate these pictures and score according to the Neonatal Skin Condition Score (NSCS). The NSCS has been widely validated for assessment of skin conditions in neonates (Lund & Osborne, 2004) and consists of three items graded from 0 to 3 with final scores ranging from 3 (perfect) to 9 (worse).

Neonatal Infant Pain Scale: Upon sensors removal, the researcher will complete the Neonatal Infant Pain Scale (NIPS) to ensure that removal of adhesive does not cause discomfort to the patient. This scale has been widely validated for the assessment of acute pain in neonates (Witt et al., 2016) and consists of six items: facial expressions, cry, breathing patters, positioning of arms and legs, and state of arousal. All items except cry, which is scored from 0 to 2, are scored from 0 to 1 based. Scores range from 0 to 7, with scores greater than 3 indicating pain.

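### The NIPS pain cut-off differs between the outcome and analysis sections at a score of exactly 3; separately, the stated NSCS item range does not fit its stated total

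*Protocol article*

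**What the plan says.** Two instruments carry the safety objective, and each is described in two places in the protocol article.

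**NIPS.** Outcomes, Objective 2 sets out six items: "All items except cry, which is scored from 0 to 2, are scored from 0 to 1 based". It then gives the range and the meaning of the total: "Scores range from 0 to 7, with scores greater than 3 indicating pain". Statistical methods, Objective 2 says that "any score of 3 or greater will be counted as indicative of pain", and that "The total number of scores of 3 or more will be reported". It adds a one-sample Wilcoxon test to "determine if the average obtained NIPS score is below 3".

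**NSCS.** Outcomes, Objective 2 says that the score "consists of three items graded from 0 to 3 with final scores ranging from 3 (perfect) to 9 (worse". Statistical methods, Objective 2 repeats the total: "NSCS scores can range from 3 = intact condition skin to 9 = very poor condition skin". The NSCS analysis takes the score at removal minus the score at baseline and tests that change against 0 with a one-sample Wilcoxon test. No NSCS threshold or count is specified.

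**The concern.** The abstract places safety within the primary outcome, and Outcomes, Objective 2 measures it by skin reactions and by pain when the sensors come off. The number of scores classed as pain is a result that the plan commits to report. With two cut-offs in the same article, a report could use either and claim to follow the protocol, and the choice could be made after the scores are known. The timing makes this practical: Participant timeline says that phase 1 enrolment started in August 2022 and that analysis runs while enrolment continues, so scores may already exist.

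For the NSCS, the stated item grades cannot produce the stated minimum total. A rater who follows the item description could record totals that the plan says cannot occur.

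**Working it through.** **1. NIPS range.** Five items graded 0 to 1 plus cry graded 0 to 2 give a minimum of 5 × 0 + 0 = 0 and a maximum of 5 × 1 + 2 = 7. The stated range of 0 to 7 is reproduced.

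**2. NIPS cut-off.**

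| Section | Rule | Scores classed as pain |
|---|---|---|
| Outcomes, Objective 2 | above 3 | 4, 5, 6, 7 |
| Statistical methods, Objective 2 | 3 or more | 3, 4, 5, 6, 7 |

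The rules differ only at a score of exactly 3. The difference between the two counts is therefore the number of scores equal to 3.

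**3. What the cut-off does not touch.** The average NIPS score and the Wilcoxon statistic against 3 are computed from raw scores, so neither depends on the pain label. The comparison value does need to match the label. Under the analysis section's rule, no pain means 2 or less, which fits a test for an average below 3. Under the outcome section's rule, a score of 3 is itself no pain, so the same test is aimed at a different boundary from the one that defines pain. In addition, the usual signed-rank test drops zero differences, so scores of exactly 3 would enter the tally as pain yet add nothing to the test.

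**4. Illustrative size.** Inputs: 24 infants per phase (Table 1); four daily sessions in phase 1; sensors replaced every 24 h over 96 h in phase 2, hence four scheduled removals (Study phases); two sensors in phase 1 and three in phase 2 (Study equipment).

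- One score per removal session: 24 × 4 + 24 × 4 = 192.
- One score per sensor removed: 24 × 4 × 2 + 24 × 4 × 3 = 192 + 288 = 480.

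The share of scores equal to 3 is not in the document; 5% to 10% is an assumption.

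| Scores | 5% equal to 3 | 10% equal to 3 |
|---|---|---|
| 192 | 9.6 | 19.2 |
| 480 | 24 | 48 |

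**5. NSCS range.** Three items graded 0 to 3 sum to between 3 × 0 = 0 and 3 × 3 = 9, so the stated minimum of 3 is not reproduced. If all three items share one range from a to b, a total of 3 to 9 needs 3a = 3 and 3b = 9, that is a = 1 and b = 3. The possible change score runs from −9 to +9 with items 0 to 3 and from −6 to +6 with items 1 to 3. The two versions also differ in the number of grades per item (four against three), so they are not the same scale with a shifted origin.

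**The case against.** The strongest reply is that an analyst has a working rule. Statistical methods, Objective 2 defines the NIPS count and states it twice, consistently; the conflict is with a descriptive sentence in the outcome section. A reader might infer from the conflict that the safety counts are undefined. The document does not support that: the one threshold count is defined where it is analysed, and the NSCS has no count at all. The analysis rule is also the more inclusive of the two, so it cannot hide a score that the other section would call pain. If the individual scores are kept, both counts can be recovered. All of this stands. It limits the harm, but it does not remove the contradiction over what a score of 3 means.

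For the NSCS, a reader might infer that baseline and removal scores could sit on different scales. Nothing suggests this. A dermatologist scores before and after photographs in pairs, and with one grading used throughout, comparing the change with 0 remains valid. The 3 to 9 total appears in both sections with matching anchors, so the item minimum looks like a slip of one digit.

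On size, a reader might take 480 as a floor for the number of NIPS scores. It is not. The text can equally mean one score per removal session. It also links NIPS to adhesive removal, whereas Study equipment says that the limb unit is held by a fabric strap. Phase 2 includes monitoring without study personnel, although the researcher completes the scale, and the Discussion foresees early discharge or transfer. Removals for care could add to the number.

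**Conclusion.** Two inconsistencies in the current text hold. The NIPS conflict is the one that matters: the status of a score of exactly 3 is contradictory, and a reported safety result moves with it. Neither the average nor the Wilcoxon test changes, though the comparison value should agree with whichever cut-off is adopted. The size is illustrative only, about 10 to 48 scores switching. It rests on the 192 to 480 scores derived from the schedule and on the assumed 5% to 10% equal to 3. The contradiction itself depends on neither figure.

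The NSCS point is a minor correction, because the score is analysed as a change from baseline and the total range is consistent across sections. The document does not settle which NIPS cut-off is right, and this review does not choose one.

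**What to change.** Reconcile Outcomes, Objective 2 and Statistical methods, Objective 2 to a single NIPS cut-off before any scores are analysed. Use it both for the count and for the comparison value of the test. Tabulate scores of exactly 3 separately so that a reader can see the count under either rule.

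In Outcomes, Objective 2, correct the NSCS item range so that it agrees with the 3 to 9 total stated in both sections; if the items share one range, that is 1 to 3. Confirm that the grading actually used matches.

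The cost is a change of wording and a check of how scores have been recorded. Rescoring arises only if photographs have already been graded with a 0 on any item. Sample size, the choice of tests and the data to be collected are unaffected.

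### The only safety results tested against a reference value are average scores, and neither test addresses how many infants were harmed

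*Protocol article*

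**What the plan says.** The analysis for Objective 2 (Statistical methods) names two tests. For skin condition: "A one sample Wilcoxon test will be performed to determine if the mean change NSCS scores" "are statistically different than 0 indicating no change in score from baseline". For pain at removal: "a one sample Wilcoxon test will be performed to determine if the average obtained NIPS score is below 3".

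The same section also plans description. Any NSCS change from baseline "will be reported as part of the sensor safety analysis". For NIPS, "any score of 3 or greater will be counted as indicative of pain", and "The total number of scores of 3 or more will be reported". Skin adverse events go on the data collection form (Device data collection forms) and to the ethics board (Data monitoring and harms).

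The Outcomes section defines pain differently: "Scores range from 0 to 7, with scores greater than 3 indicating pain". On size, the Sample size section says "A convenience sample size of 48 neonates was determined, 24 infants for each phase". The article states no significance level, margin or unit of analysis for the two safety tests.

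**The concern.** Safety is part of the primary outcome in the Abstract and is Objective 2. The question for a skin-mounted sensor is how many infants have worse skin or a painful removal. A test on the centre of a score distribution does not answer it.

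- **NIPS.** The test can support a value below 3 when many removals are painful, provided enough score low.
- **NSCS.** It is a difference test with no margin, on a sample with no power basis. A non-significant result therefore cannot support safety. Unchanged sites drop out of the signed-rank calculation, and improvements offset deteriorations.

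Both tests are also described as tests of a mean or average, which the signed-rank test is not. If several scores per infant are pooled, its independence assumption fails. The results most likely to be cited as safety evidence could then sit beside substantial harm.

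**Working it through.** The article gives no figure to reproduce for these tests.

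**Inputs.** From the article: 48 infants, 24 per phase; NIPS reference value 3; NSCS reference value 0; a NIPS score of 3 or more counted as pain in the analysis section. Assumed: one score per infant, NIPS tested one-sided, NSCS tested two-sided at 0.05, exact signed-rank test with zero differences dropped. Score patterns are illustrative.

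**NIPS, half the infants at 5.** 24 infants at 5 (difference +2) and 24 at 0 (difference −3).
- Mid-ranks: 12.5 for the smaller differences, 36.5 for the larger.
- Positive rank sum: 24 × 12.5 = 300. Expected under the null: (48 × 49/2)/2 = 588.
- Variance: (24/4) × (12.5² + 36.5²) = 8,931, so SD = 94.5.
- z = (300 − 588)/94.5 = −3.05; one-sided p = 0.001 (exact 0.0012).

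**NIPS, a third in pain.** 16 infants at 4 or 5 and 32 at 0 or 1: mean 1.83, exact one-sided p = 0.00001.

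**NIPS, most at exactly 3.** 42 infants at 3 and 6 at 0. The 42 zero differences drop out, leaving 6 negative ones: p = 1/2⁶ = 0.016. By the analysis section's definition, 42/48 = 87.5% are in pain. By the Outcomes definition, none is.

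**NSCS, nobody improves.** With k worsened infants, two-sided p = 2/2ᵏ.

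| k | p | of 24 | of 48 |
|---|---|---|---|
| 4 | 0.125 | 16.7% | 8.3% |
| 5 | 0.0625 | 20.8% | 10.4% |
| 6 | 0.031 | 25.0% | 12.5% |

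The exact 95% interval for 5/48 is 3.5% to 22.7%.

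**NSCS, some improve.** With 1-point changes, 16 worse and 6 better of 48 gives 2 × P(Bin(22, 0.5) ≤ 6) = 0.052, with a third of infants worse.

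**Pooled scores.** If each sensor is scored once per day, phase 1 gives 2 × 4 = 8 scores per infant and phase 2 gives 3 × 4 = 12, or 480 in all. This is an assumption.
- Size-weighted cluster size: (24 × 8² + 24 × 12²)/480 = 10.4.
- Variance inflation 1 + 9.4ρ: 1.94, 3.82 and 5.70 for ρ = 0.1, 0.3 and 0.5.
- Two-sided error 2Φ(−1.96/√inflation): about 16%, 32% and 41% against a nominal 5%. Simulation gave 15–16%, 29–31% and 40–41%.
- One-sided, as for NIPS, simulation gave about 11%, 20% and 23%.

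**What a proportion would show.** The exact upper limit for zero events is 1 − 0.025^(1/n): 7.4% for 0/48, 14.2% for 0/24 and 46% for 0/6.

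**The case against.** A reader might infer that the protocol judges safety by these two tests and would declare the sensor safe on their result. The documents do not support that. No section contains such a rule, the NIPS test is introduced as an addition to the reported average and count, and skin events are recorded and submitted separately. In the half-in-pain example, the report would also show 24 painful scores.

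A reader might also take the NSCS sentence to mean that non-significance will be read as no change. The more natural reading is that the value 0 denotes no change; no rule for a non-significant result is given.

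Nor does the NSCS test, by itself, hide a large minority. If nobody improves, it becomes significant at 6 worsened infants; with an uncorrected normal approximation, at 4 (p = 0.046). Hiding more requires offsetting improvements, possible only where the baseline score is above the scale's floor of 3. If sites are scored separately, five infants each worsening at two sites give 10 same-direction changes and p = 2/2¹⁰ = 0.002. Pooling also makes the NSCS test flag change more often, so the error there does not run towards missed harm. The error rates rest on an unstated unit and assumed correlations.

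Finally, this is an exploratory observational study, and a condensed article may leave denominators and intervals to an analysis plan. That is fair for the details. It does not cover the choice of what is tested, which the article fixes.

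**Conclusion.** The point holds in a limited form. The only safety comparisons with a reference value concern averages, and the planned counts carry no stated per-infant denominator or interval.

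The NIPS part is the stronger. A significant result is compatible with a third to a half of infants in pain, and the test drops scores of exactly 3 that its own section counts as pain. The NSCS part is narrower: a non-significant result is compatible with 5 of 48 infants worsening, or more if others improve, so it is not evidence of no harm. Pooling repeated scores would invalidate the p-values, but whether that is planned cannot be told from the article.

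These sizes depend on one score per infant, the assumed sidedness and significance levels, exact tests and illustrative score patterns. The conclusion that neither test measures the proportion harmed does not.

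**What to change.** 1. Reconcile the NIPS pain definition between the Outcomes section (above 3) and the analysis section (3 or above) first, because the pain proportion depends on it.
2. Make the main safety summary two infant-level proportions: infants with any NSCS worsening at any site, and infants with any removal meeting the reconciled pain definition. Give each an exact 95% interval, overall and by phase.
3. Report the share of painful removals with an interval that allows for clustering within infant, and state the unit of analysis.
4. Keep average scores and age-group results as description. Groups 1 and 2 have 6 infants each per phase in Table 1, so intervals at that level say little.
5. Draw no safety conclusion from the Wilcoxon tests.

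The planned scores suffice, and only analysis wording changes. The price is a more cautious safety statement: with no events at all, the upper limit is still 7.4% overall and 14.2% in a phase.

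### The only pain test compares the average NIPS score with 3, so it does not address how many infants have pain at sensor removal and can be significant when a quarter of them do

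*Protocol article*

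**What the plan says.** In the Outcomes section, Objective 2, the NIPS is completed when sensors come off, and its purpose is given as "to ensure that removal of adhesive does not cause discomfort to the patient". The same paragraph defines pain: "Scores range from 0 to 7, with scores greater than 3 indicating pain".

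Under Statistical methods, Objective 2, the scores are part of the safety assessment: "Safety will also be assessed by evaluating the subjective pain scores obtained with the NIPS results". Three outputs follow:

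- the average score;
- a count, with pain defined as "any score of 3 or greater will be counted as indicative of pain" and the commitment "The total number of scores of 3 or more will be reported";
- a test: "a one sample Wilcoxon test will be performed to determine if the average obtained NIPS score is below 3".

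The test is the only inferential pain analysis. The article gives no significance level, sidedness, expected score distribution or acceptable pain rate. On size it says "A convenience sample size of 48 neonates was determined, 24 infants for each phase".

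**The concern.** The cut-off of 3 classifies one score at one removal. The test carries it over to the location of all scores together. On a 0 to 7 scale, many scores of 0 to 2 can outweigh a sizeable minority in the pain range. A location clearly below 3 therefore does not show that few infants had pain.

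The purpose given in the Outcomes section concerns the individual patient, and it calls for the share of infants who had pain. That share gets only a total, with no stated denominator or interval, while the p-value goes to a quantity that does not answer the question. At stake is how the pain part of a named safety objective will read: a small p-value could stand beside a pain rate that a neonatal unit would want to see estimated.

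There is also a technical problem. A score of exactly 3 counts as pain in the analysis section but equals the null value of the test. The usual signed-rank handling drops such zero differences, so these scores never count against the device.

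**Working it through.** The article states no figure for this test, so there is nothing to reproduce. The check asks what the test returns when a known share of infants is in the pain range.

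**Inputs from the article.** Null value 3; direction of interest below 3; scale 0 to 7; 48 infants, 24 per phase.

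**Assumptions.** One independent score per infant; one-sided 0.05 (0.025 also checked); score distributions as shown. Painful scores in steps 1 to 3 are 4 or more, so they count as pain under both stated cut-offs.

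**1. Worked example, n = 48.** Twelve infants score 5, and twelve each score 0, 1 and 2.

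- Mean = (12×5 + 12×0 + 12×1 + 12×2)/48 = 96/48 = 2.0.
- Differences from 3: twelve each of +2, −3, −2 and −1.
- Mid-ranks of the absolute differences: 6.5 for 1 (12 values), 24.5 for 2 (24 values), 42.5 for 3 (12 values).
- Positive rank sum = 12×24.5 = 294. Total = 1,176, so the null expectation is 588.
- Null SD = √(Σr²/4) = √(36,588/4) = 95.6.
- z = (294 − 588)/95.6 = −3.07, one-sided p = 0.001 (exact permutation p = 0.0008).
- In the pain range: 12/48 = 25%, Clopper-Pearson 95% CI 13.6 to 39.6%.

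**2. Sensitivity of the example.** Twelve of 48 are in pain throughout; exact one-sided p.

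| Painful scores | Other scores | p |
|---|---|---|
| all 4 | even over 0, 1, 2 | <0.00001 |
| all 5 | even over 0, 1, 2 | 0.0008 |
| all 6 | even over 0, 1, 2 | 0.059 |
| all 7 | even over 0, 1, 2 | 0.22 |
| all 5 | all 2 | 0.21 |

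**3. Simulated chance of a significant result.** Non-painful scores 0/1/2 at 60/25/15%, one-sided 0.05.

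| True pain rate | Painful scores | n = 48 | n = 24 |
|---|---|---|---|
| 25% | 4 to 5 | 100% | 98% |
| 25% | 4 to 7 | 93% | 71% |
| 25% | 6 to 7 | 42 to 45% over repeat runs | about 32% |
| 30% | 4 to 7 | 78% | 53 to 55% over repeat runs |

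The expected mean in the second row is 0.25×5.5 + 0.75×(0.25×1 + 0.15×2) = 1.79. At one-sided 0.025 that row becomes 87% and 61%. With the other scores uniform over 0 to 2, the row for 6 to 7 becomes 35% and 27%.

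**4. Scores of exactly 3.** Suppose 40 of 48 infants score 3 and 8 score 2. The 40 zero differences drop out and the remaining 8 are all negative, so exact one-sided p = 0.5⁸ = 0.004. The analysis section's own definition puts 40/48 = 83% in pain. The average is (40×3 + 8×2)/48 = 2.83, so the statement that it is below 3 is true but uninformative.

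**5. Precision of the proportion.** 12/48: 13.6 to 39.6%. 6/24: 9.8 to 46.7%. With no events the upper limit is 1 − 0.025^(1/n): 7.4% for 0/48 and 14.2% for 0/24.

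**The case against.** A reader might infer that removal would be declared safe whenever this test is significant. The article does not say so. It lists the average and the count first and adds the test to them, and it attaches no decision to the p-value. Because the count of pain-range scores is reported, a 25% rate would be visible. Safety also rests on skin scoring and adverse event reporting.

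A reader might also infer that the test almost cannot fail at worrying pain rates. The calculations do not support that. When painful scores are 6 or 7, fewer than half of trials reach significance at a 25% rate, and at n = 24 even the spread over 4 to 7 misses in about 29%. The score distributions, the significance level and the 25% itself are assumptions.

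Finally, a denominator, an interval and per-infant summaries are details that a condensed article may leave to its analysis plan, and this is an observational convenience-sample study that describes itself as exploring feasibility.

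All of this limits the point and lowers its weight. It does not remove it. The article does fix its one pain test, and fixes it on the average. The missing interval alone would not be a finding; a stated test aimed at a quantity that does not match the stated purpose is.

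**Conclusion.** The point holds in limited form. The only inferential pain analysis applies a per-score cut-off to an average and leaves open how many infants have pain at removal. It can be clearly significant with a quarter of infants in the pain range when painful scores are moderate or spread out, and often is not when they are mostly 6 or 7. The simulated range at a 25% rate with the 60/25/15% split is about 42 to 100% for 48 infants and about 32 to 98% for 24, under independent single scores and one-sided 0.05. The loss of scores of exactly 3 needs no assumed spread, only the usual handling of zero differences and the cut-off in the analysis section.

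Pain is not hidden, and no rule turns the p-value into a safety verdict. The analysis should be corrected, but the defect does not undermine the study.

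**What to change.** 1. Reconcile the pain cut-off. The Outcomes section places pain above 3, whereas Statistical methods includes 3. No pain proportion is defined until one reading applies throughout.
2. Make the main pain result the proportion of infants with at least one removal in the pain range, with an exact 95% interval, overall and by phase.
3. Add the proportion of removals in the pain range with an interval that allows for clustering within infant, because sensors are removed repeatedly over the four days.
4. Keep the average as description and draw no safety conclusion from the Wilcoxon test.

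The cost is one paragraph of analysis text, using data already planned. The downside is a less favourable result with a wide interval: even with no painful removal, the upper limit is 7.4% for 48 infants and 14.2% for 24. The article sets no acceptable rate, so the proportion should be presented as an estimate and not as a pass or fail.
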